#### Data analysis and statistical analysis.

The following values from the NIRS device will be used to assess both aims: 1) mitochondrial capacity change over time (chemotherapy cycle) and 2) between drug regimens. Previous literature has shown that oxygenation levels at rest after moderate and/or high intensity exercise or after occlusion follows an asymptotic curve of the form [54]:

$$\begin{array}{c} y=A+\left(B_{0}-A\right)e^{-\tau /t} \end{array}$$
(1)

Where *y* is the oxygenation at time *t*, *A* is the oxygenation as *t* approaches infinity*, t* is time measured in seconds, B_*0*_ is the value at *t = 0*, and *τ* is the time constant. For each rest period, we will run an asymptotic regression for O2Hb, HHb, and TSI by time in seconds to find the coefficient estimate for *τ*.

Each data set will contain three rest periods; therefore, each data set will have three *τ* values for each variable. We will average the τ values to obtain one average rest τ for O_2_Hb, HHb, and TSI per data set. Since continuous wave NIRS devices measure oxy- and deoxyhemoglobin as changes from baseline, raw oxy- and deoxyhemoglobin values will have no meaning and are not comparable except when measured as changes over time or as τ values.

We will analyze the *ΔO*_*2*_*Hb,* Δ*HHb,* and *ΔTSI*, calculated as the change in steady state levels of O_2_Hb, HHb, and TSI respectively from work to rest, with steady state values calculated as the mean value of the final thirty seconds of the stage. For each data set of one on-off kinetics, there will be three work/rest period pairs therefore we will calculate three delta values and average the three delta values to obtain one delta value for O_2_Hb, HHb, and TSI per data set. The three work/rest transitions will allow for reliability testing with intraclass correlation coefficients. For participant data to be included in the final analysis, the participant will need to complete at least three on-off kinetic laboratory visits. Each participant will complete an on-off kinetics at least two weeks apart, but not more than one month apart in accordance with their prescribed chemotherapy treatment regimen. Each on-off kinetics will correspond with the first infusion of a chemotherapy cycle. To allow participants a maximum amount of time to recover from infusions before participating in exercise, the corresponding on-off kinetics takes place within 48 hours of the first infusion of the subsequent chemotherapy cycle. Since chemotherapy treatments vary depending on oncologist recommendation, each participant may complete different lengths of treatment, resulting in each participant having different numbers of data points. This will prevent us from using traditional statistical analysis such as repeated measures ANOVA. Since it is not time itself, but rather the compilation of chemotherapy infusions over time that we predict will cause changes in measures of mitochondrial oxidative function, we will treat the number of chemotherapy cycles as an ordinal variable in this analysis. We will complete an analysis using mixed effects models to predict τ and deltas from the number of chemotherapy treatments with a random intercept for patients. For aim 2, ANOVAs will be used to assess differences in mitochondrial capacity between drug regimens at each chemotherapy cycle.

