### Sample size

We conducted a power analysis using Monte Carlo data simulation. We conducted the analysis using a mixed effects model with a fixed effect of chemotherapy cycle (time) and random effects for slope and intercept by participants with unstructured correlation [33–36]. Cheng [35] et al. suggest the use of unstructured correlation when time is used as a fixed effect (chemotherapy cycle) and we are not making specific assumptions about the shape of the curve. Due to limited studies of NIRS measurements of patients with cancer, we used the conservative estimate of average recovery kinetics time constant (τ) of patients with chronic heart failure (25.35 seconds) and extrapolate average change in τ throughout chemotherapy from Foulkes using results from Beever [37,38]. We assume that the random intercept will follow a gamma distribution with shape 1.57, a scale of 12.5, and a right shift of 13.25. Additional assumptions from Foulkes [38] and Beever [37] include the random slope is assumed to follow a normal distribution with an extrapolated standard deviation, as well as a normal distribution of the error with standard deviation of 5.54 [39,40]. Analysis indicates that using a linear mixed effects model with sample size of at least n = 30 will be able to detect an effect of chemotherapy on τ with a power of 0.8. Due to potential dropout or missing data, data collection will continue until data is collected on 30 subjects who have completed the study. As the effect of chemotherapy type on τ is unknown and unable to be approximated with data simulation, we are unable to conduct a full power analysis with the effect of chemotherapy type on τ [29,41,42]. Based on treatment regimens of pilot data, chemotherapy type can be divided into cytotoxic (platinum-based, anthracyclines, etc.) for 3–4 cycles and non-cytotoxic such as immunotherapy for an additional 3–4 cycles. In some cases, treatment would be given concurrently and could be treated as a separate group of cytotoxic + non-cytotoxic. We assume that at least n = 8 of each chemotherapy type will be necessary to detect any differences in trajectory of τ over time consisting of 3 or more cycles of chemotherapy Comparisons between drug regimens could be adjusted based on updates to the NCCN guidelines.

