### Observational protocol for first and subsequent visits

Before starting chemotherapy, patients will undergo baseline testing that includes a lactate threshold test and an ON-OFF kinetics exercise test. The lactate threshold test will determine the power output (110% power at lactate threshold, P_LT+_) to be used for the follow-up baseline on-off kinetics test (ON-OFF). The ON-OFF kinetics test will take place at least 24 hours after the lactate threshold test and consist of 3 cycles of 2 minutes at P_LT+_ and 2 minutes of complete rest. Whole body O_2_ uptake and CO_2_ production will be captured via a metabolic cart during each test. Testing will take no more than 60 minutes per session, with a maximum study total of 300 minutes (about 5 hours) of participation per patient. Patients will be requested to avoid exercise and use of certain substances (tobacco, alcohol, caffeine, and contraindicated medications) 24 hours before testing. If laboratory baseline evaluation cannot be completed prior to the participant’s treatment initiation, treatment will not be delayed, and patients will be waived from the study.

The independent variables in this study are drug regimen and number of chemotherapy treatments. The dependent variables in this study will be the changes in O_2_Hb, HHb, and TSI of the vastus lateralis, indicative of mitochondrial oxidative capacity after a bout of cycling. The specific variables measured will be the average recovery kinetics time constant, τ, and TSI. Indirect calorimetry (O2 uptake, CO2 production) also will be captured at rest and during the ON/OFF kinetics as control variable comparisons for whole-body O2 uptake and utilization.

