#### Visit #2 + : On-off kinetics testing.

Using the reference photo taken at the first visit, mark the NIRS device location and use the ultrasound to measure and record ATT. If the ATT measurement matches the ATT from the first visit, secure the NIRS device with tape as previously described. The participant will fill out the BFI, PROMIS Global Health, and Physical Activity Follow Up forms and update contact information if needed.

The participants will sit on the bike for a two-minute rest. Participants will begin pedaling for a warmup at 0 Watts for 2 minutes at a self-selected steady cadence of 60–100 RPM. After the 2-minute warm up, the power output will increase to P_LT+_. Participants will cycle at the same self-selected cadence for 2 minutes (“on-kinetics’‘). Thirty seconds before the end of the on-kinetics stage, participants will be asked their RPE. At the end of the 2-minute on-kinetics period, participants will stop pedaling and study staff will remove their non-measured leg from the pedal to rest on a box in a relaxed, extended position to aid in total relaxation and remove any additional movement of the measured leg. During the rest period, participants will remain in recovery sitting on the bike for 2 minutes (“off-kinetics’‘ stage). Participants subsequently will start pedaling at their self-selected cadence for their next 2 minute “on-kinetics” stage, followed by another 2-min “off-kinetics’‘ period. This cycle of exercise followed by rest, referred to as on-off kinetics, will repeat for a total maximum of 3 times, or unless the patient requests to stop.

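### Equation (1) prints the exponent as −τ/t, which contradicts the article's own definitions of A, B0 and τ; it should read −t/τ, and the fitting code should be checked against it.

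*Protocol article*

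**What the plan says.** In the protocol article, the section Data analysis and statistical analysis gives the recovery curve as equation (1), y = A + (B0 − A)·e^(−τ/t). The sentence after it defines the terms:

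- A "is the oxygenation as *t* approaches infinity".
- B0 "is the value at *t = 0".
- τ "is the time constant".

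The model is then applied to each rest period: "we will run an asymptotic regression for O2Hb, HHb, and TSI by time in seconds to find the coefficient estimate for" τ. The three τ values of a session are averaged. No other place in the article gives the equation in another form.

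The section on first and subsequent visits names τ as an outcome: "The specific variables measured will be the average recovery kinetics time constant, τ, and TSI". The Sample size section plans on the "average recovery kinetics time constant (τ) of patients with chronic heart failure (25.35 seconds"). The last part of the analysis section models τ and, separately, the changes ΔO2Hb, ΔHHb and ΔTSI. These changes are computed from means over the last thirty seconds of each stage.

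**The concern.** The displayed equation and the definitions beside it cannot both be right. If the definitions hold, the curve starts at B0 and settles at A. The printed exponent does the opposite and cannot be evaluated at the point where B0 is defined.

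The equation matters because it is the only statement of how τ is computed, and τ is both an analysed outcome and the quantity on which the study was powered. Anyone who codes equation (1) as printed, whether the study team or a group reusing the protocol, would estimate a different quantity under the same name. It could not be compared with the planning value of 25.35 s or with time constants from other studies.

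**Working it through.** **Inputs from the article.** The printed equation and the definitions of A, B0 and τ come from Data analysis and statistical analysis. The planning value of 25.35 s comes from Sample size. The fit window follows from the recovery period in Visit #2+ ("participants will remain in recovery sitting on the bike for 2 minutes", so 120 s). The sampling rate of 10 Hz comes from Collection of biometrics at each visit.

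**Assumptions, not in the article.** TSI recovers from B0 = 45 to A = 60, without noise. The limits in step 1 do not depend on these levels. Repeating the fits with levels of 50 and 70 gave the same τ estimates.

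**Step 1: limits of the printed form (τ > 0).**

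- t → 0+: τ/t → ∞, so e^(−τ/t) → 0 and y → A. The article says B0.
- t → ∞: τ/t → 0, so e^(−τ/t) → 1 and y → B0. The article says A.
- t = 0: division by zero, so the expression is undefined.

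**Step 2: limits with exponent −t/τ.**

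- t = 0: e^0 = 1, so y = B0.
- t → ∞: e^(−t/τ) → 0, so y → A.
- t = τ: 1 − e^(−1) = 63% of the recovery is complete, which is what a time constant means.

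All three definitions hold.

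**Step 3: the two forms in numbers (τ = 25.35 s, A = 60, B0 = 45).**

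| t (s) | −τ/t (printed) | −t/τ |
|---|---|---|
| 0.1 | 60.0 | 45.1 |
| 10 | 58.8 | 49.9 |
| 25.35 | 54.5 | 54.5 |
| 60 | 50.2 | 58.6 |
| 120 | 47.9 | 59.9 |

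With the parameters as defined, the printed curve falls where it should rise. The two agree only at t = τ.

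**Step 4: what a literal fit would return.** Curves were generated from y = 60 − 15·exp(−t/τ), t = 0.1 to 120 s at 10 Hz. The printed form was fitted by nonlinear least squares with A, B0 and τ all free.

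| True τ (s) | Fitted τ (s) | Shortfall | Fitted A | Fitted B0 |
|---|---|---|---|---|
| 13.25 | 7.20 | 46% | 46.1 | 61.3 |
| 20 | 12.11 | 39% | 46.4 | 61.8 |
| 25.35 | 16.16 | 36% | 46.5 | 62.1 |
| 40 | 26.53 | 34% | 46.6 | 62.4 |
| 60 | 37.60 | 37% | 46.5 | 61.9 |

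For 25.35 s: 1 − 16.16/25.35 = 0.36. A and B0 exchange roles: A lands near the start level and B0 near the plateau. The residual error is small, with a root mean square of 0.23 to 0.32 TSI points on a 15-point recovery and R² of about 0.99 or higher. Goodness of fit alone would therefore not expose the error; the swapped A and B0 would.

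**Step 5: dependence on the setup (true τ = 25.35 s).**

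- All parameters free, window 30, 60, 120 or 180 s: fitted τ = 13.0, 16.5, 16.2 or 14.7 s.
- A and B0 held at their defined values, 120 s window: fitted τ is about 363 s, with a very poor fit (root mean square error about 4.9 TSI points).

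Neither the direction nor the size of the error is fixed. Both depend on how the literal form is fitted. Fitting exp(−t/τ) to the same kind of curve returns the true 25.35 s.

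**The case against.** The strongest reply is that this is a transposition of two symbols, and that the text around the equation already settles the method. It calls the curve asymptotic, defines A as the limit at infinity and B0 as the starting value, calls τ a time constant, and says "we will run an asymptotic regression for O2Hb, HHb, and TSI by time in seconds". Of the two exponents, only −t/τ satisfies all of that. A statistician following the words, or using a standard asymptotic regression routine, would fit the right model. No code and no τ results appear in the article. This stands, and it makes any harm conditional. It does not rescue the equation, which is the only formula given for τ and is wrong by its own definitions.

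A reader might infer three stronger things that the article does not support:

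- **That the data of the 26 completed participants have been analysed with the wrong curve.** Nothing in the article shows which form was coded.
- **That every analysis for both aims is affected.** The delta outcomes are also modelled and come from steady-state means, not from equation (1).
- **That the sample size is wrong for this reason.** The simulation, as described, specifies distributions for τ directly and does not use the recovery equation.

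Nor is the shortfall of 34–46% a property of the plan. It belongs to one way of fitting the printed form, and step 5 shows a very different result under another.

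**Conclusion.** Equation (1) is wrong as printed. This follows from the article alone, with no assumption: the exponent −τ/t reverses the stated roles of A and B0, is undefined at t = 0, and does not make τ a time constant. The point deserves correction rather than being passed over as a background misprint, because it is the sole definition of an analysed outcome that is also the variable used in the power analysis.

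The consequence for results is conditional. If the printed form were fitted literally, τ would be wrong: 34–46% too low over true values of 13.25 to 60 s under the illustrative setup, or about 363 s for a true 25.35 s with A and B0 fixed. If the code already uses the standard exponential, the results are unaffected and only the text needs changing.

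**What to change.** Replace equation (1) with y = A + (B0 − A)·exp(−t/τ), and state that t = 0 is the end of each work bout. Check that the R code used for the completed participants fits this form, or an equivalent rate form with the rate converted to τ. A quick diagnostic is whether fitted A lies near the end-of-rest level and fitted B0 near the end-of-work level; if they are exchanged, the printed form was fitted. Refit only in that case.

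The cost is a one-line correction and a code check. No new data are needed, and the delta analyses and the sample size do not have to be revisited on this account.

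### The last 30 s of a 2-minute rest is not a full plateau for slower patients, so ΔO2Hb, ΔHHb and ΔTSI shrink modestly when τ lengthens

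*Protocol article*

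**What the plan says.** The on-off kinetics section fixes the rest stage: "participants will remain in recovery sitting on the bike for 2 minutes". Under Data analysis and statistical analysis, Δ is the difference between the work and rest levels, "with steady state values calculated as the mean value of the final thirty seconds of the stage". The three work/rest pairs of a visit are then combined: "average the three delta values to obtain one delta value for O_2_Hb, HHb, and TSI per data set". The mixed models take both τ and the deltas as outcomes predicted from the number of chemotherapy treatments.

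The same section models each recovery as an asymptotic curve in which A "is the oxygenation as *t* approaches infinity", and for each rest period "we will run an asymptotic regression for O2Hb, HHb, and TSI by time in seconds to find the coefficient estimate" of τ. A is thus estimated for every rest period, but Δ does not use it.

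The Sample size section gives two descriptions of τ. One is the "conservative estimate of average recovery kinetics time constant (τ) of patients with chronic heart failure (25.35 seconds"). The other is that the "random intercept will follow a gamma distribution with shape 1.57, a scale of 12.5, and a right shift of 13.25".

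**The concern.** An exponential recovery has reached a plateau by 90 s only if τ is short relative to 90 s. For a patient with a long τ, the signal is still moving towards A throughout the window (upwards for O2Hb and TSI, downwards for HHb). The last-30-s mean then understates the size of the change from work to rest. The shortfall depends on τ, and τ is what the study expects chemotherapy to alter.

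If τ lengthens over cycles, Δ will shrink somewhat even when the true amplitude has not changed. A report that both worsened could be read as two separate signs of mitochondrial decline when part of the second follows arithmetically from the first. The same applies under aim 2 if Δ is compared between regimens that differ in recovery speed. Averaging the three pairs reduces noise but not this bias, because all three share the same window.

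**Working it through.** **Inputs from the protocol.** Rest stage 120 s; window 90 to 120 s; stated average τ 25.35 s; patient τ distributed as 13.25 + gamma(shape 1.57, scale 12.5); exponential approach to A.

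**Assumptions.** The Sample size τ applies to all three signals, recovery is mono-exponential without delay, and the work level does not depend on τ. The standard form e^(-t/τ) is used. Eq. 1 as printed has e^(-τ/t), which tends to 1 as t grows, so y would tend to B0 and not to A. That contradicts the protocol's own definition of A.

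**Step 1: the plan's own average τ.** The printed gamma has mean 13.25 + 1.57 × 12.5 = 32.875 s, median 28.9 s and mode 13.25 + 0.57 × 12.5 = 20.4 s. None of these is 25.35 s, so the stated average is not reproduced.

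**Step 2: unrecovered share.** Averaging e^(-t/τ) over 90 to 120 s gives

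R(τ) = (τ/30) × (e^(-90/τ) − e^(-120/τ)), and measured Δ = (1 − R) × true Δ.

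| τ (s) | e^(-90/τ) | e^(-120/τ) | R |
|---|---|---|---|
| 25.35 | 0.0287 | 0.0088 | 1.7% |
| 32.875 | 0.0647 | 0.0260 | 4.2% |
| 40 | 0.1054 | 0.0498 | 7.4% |
| 50 | 0.1653 | 0.0907 | 12.4% |
| 60 | 0.2231 | 0.1353 | 17.6% |

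**Step 3: how many patients.** R exceeds 5% when τ > 34.7 s and 10% when τ > 45.2 s. The gamma can be matched to a mean of 25.35 s by changing its scale to (25.35 − 13.25)/1.57 = 7.71, or its shift to 25.35 − 19.625 = 5.725.

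| τ distribution | R > 5% | R > 10% |
|---|---|---|
| As printed | 35% (about 11 of 30) | 18% (about 5 of 30) |
| Scale changed to 7.71 | 15% | 4% |
| Shift changed to 5.725 | 22% | 11% |

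Under the printed gamma the mean of R is 5.3% and its median 2.8%.

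**Step 4: mechanical effect on Δ.** With the amplitude fixed, the relative change is (1 − R(τ + d))/(1 − R(τ)) − 1. The protocol does not print its expected change in τ, so d = 5 s and d = 10 s are assumptions. From 25.35 s, a 10 s slowing gives R(35.35) = 5.3% and a change of 0.947/0.983 − 1 = −3.7%. From 50 s it gives 0.824/0.876 − 1 = −5.9%. Averaged over the printed gamma, Δ falls by 1.9% for 5 s and 4.1% for 10 s.

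**Step 5: is A a better rest level?** Simulated 120 s recoveries at 10 Hz were used, with assumed autocorrelated noise of SD 3% to 5% of the amplitude and averages of three rests. From τ = 20 to 50 s, the root-mean-square error of A was at or below that of the last-30-s mean in all settings I rechecked. At 60 s it was lower in all but the noisiest, most strongly autocorrelated setting, where a few fits ran away. Another run with noise SD 5% put the single-rest SD of A at τ = 50 s as high as 0.28 of the amplitude. Over three rests that is 0.28/√3 = 0.16, more than the 12.4% bias it would remove. A's advantage therefore depends on the noise.

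**The case against.** The last-30-s mean is transparent and needs no curve fit. At the stated average τ the shortfall is only 1.7%, and the median patient under the printed gamma is about 97% recovered. The larger shares come from a distribution that conflicts with the stated average. The average τ is borrowed from chronic heart failure, whereas Table 1 excludes clinically advanced cardiovascular disease and requires a minimum activity score, so the slow tail may be thinner in this cohort. The protocol gives no expected effect or variance for Δ, so nothing shows that a 2% to 4% shift would change a conclusion. All of this stands, and it limits the point to a modest one.

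The objection to the remedy also stands in part. A and τ come from the same fit, so their errors are correlated: in simulation 0.68 to 0.79 at τ = 25.35 s and 0.94 to 0.99 at 50 s, against 0.51 to 0.58 and 0.15 to 0.50 for the last-30-s mean. Using A removes the systematic bias but ties the estimation errors more closely. This is why both versions should be shown, and not one put in place of the other.

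A reader might infer that most Δ values are unusable, that a fall in Δ would be mainly artefact, or that any τ above 30 s rules out a steady state. The documents support none of these. The shortfall at 30 s is about 3%, and no particular cut-off follows from the plan. Nor is the τ analysis or its sample size touched, because τ does not depend on how Δ is computed.

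**Conclusion.** The point holds in a limited form. Under the plan's own recovery model the last-30-s value is not a full plateau for slower patients, and Δ falls whenever τ lengthens. The link is small for a typical patient and matters mainly in the slow tail, where the shortfall exceeds 10% of the amplitude in 4% to 18% of patients depending on which τ distribution is meant. These are planning figures, not observed properties of the cohort, and they rest on the assumptions listed in the working. What follows is that a joint change in τ and Δ should not be presented as two independent findings, and that the two descriptions of τ in the Sample size section need reconciling. This is a cheap improvement to a secondary measure, not a threat to the powered outcome.

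**What to change.** - Correct Eq. 1 to e^(-t/τ), so that A is the level approached as t grows.
- Compute Δ for each signal with the fitted A of that rest period as the rest level, and keep the mean of the final 30 s of work as the work level. Report this beside the last-30-s Δ for all participants. Use the last-30-s value where the fit does not converge, and say in advance how a runaway fit is recognised.
- Do not call the last-30-s value a steady state without a plateau check. No fixed 30 s cut-off on τ is needed.
- Treat a joint change in τ and Δ as separate evidence only if the A-based Δ also changes, and acknowledge that errors in A and τ are correlated.
- Reconcile the average τ of 25.35 s with the printed gamma, whose mean is 32.9 s.

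The cost is a few sentences of analysis text. A is already estimated for every rest period, so no new data or visits are needed, and the 26 participants who have completed can be reanalysed. The downside is that A is noisier when τ is long. Settling the rule before the final analysis avoids choosing between the two versions after seeing results.

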Assessment of mitochondrial capacity with NIRS includes studies of clinical populations with peripheral artery [27], chronic kidney [24], and neurologic diseases such as traumatic spinal cord injury and multiple [22], as well as comparisons with healthy [28] and age-related differences in skeletal muscle oxidative [17]. However, there is a dearth of NIRS studies examining the effects of chemotherapy on skeletal muscle mitochondrial function in patients with cancer. Only two studies to our knowledge have utilized NIRS to measure muscle oxygenation variables in cancer survivors. Ederer, et al. [29] determined that [HHb] and [Hb]total were significantly lower in eight cancer survivors (all eight received chemotherapy and five received radiation) compared to healthy controls during exercise at ventilatory threshold. Grigoriadis et al. [30], did not find a significant difference in muscle oxygenation variables between 23 patients with breast cancer (16 received chemotherapy, nineteen received radiation therapy, and 21 received hormonal therapy) and 23 participants who served as age and BMI matched controls. Recent literature of near infrared spectroscopy related to cancer primarily involves detection and identification of cancerous [31] or the use of near infrared light as a photoimmunotherapy [32]. Therefore, the hypothesized loss of mitochondrial capacity throughout chemotherapy treatment has not been studied longitudinally starting at baseline and tracking through the chemotherapy regimen in breast and gynecologic cancer patients with NIRS to date.

The aims of our study are to develop a protocol that 1) assesses mitochondrial dysfunction in cancer patients using exercise that is tolerable for the patients throughout the entire chemotherapy regimen and 2) observe the changes in mitochondrial functional capacity between different chemotherapy regimens for each chemotherapy cycle. The protocol also will help us evaluate a potential correlation between subjective self-reported fatigue and perceived effort with corresponding objective whole-body metabolic measurements and NIRS measurements. The proposed study will help inform clinical decision makers in the oncology community regarding current chemotherapy regimens (based upon the National Comprehensive Cancer Network, NCCN) that patients may best tolerate for cachexia and fatigue.

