### Trial status

The trial is currently in the data collection phase with 26 participants who have completed the protocol. The study is planned to continue to enroll test subjects until n = 30.

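### Analysing only patients with at least three on-off tests selects on attendance after baseline; if stopping is related to τ, deterioration is liable to be understated

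*Protocol article*

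**What the plan says.** Two statements in the protocol article act together.

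- Data analysis and statistical analysis: "For participant data to be included in the final analysis, the participant will need to complete at least three on-off kinetic laboratory visits". No reason is given for the threshold.
- Sample size: after the words "Due to potential dropout or missing data", the article says that "data collection will continue until data is collected on 30 subjects who have completed the study". Participants who do not complete are in effect replaced.

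The data analysis section also explains that patients will have unequal numbers of tests because regimens differ in length. It gives this as the reason for mixed effects models instead of repeated measures ANOVA. The model it names has a random intercept for patients. The power analysis in the sample size section uses a random intercept and a random slope.

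The discussion expects conditioning to fall as treatment progresses. The introduction describes the test as "using exercise that is tolerable for the patients throughout the entire chemotherapy regimen", and the discussion names feasibility of longitudinal NIRS testing as a purpose of the pilot.

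**The concern.** Whether a patient reaches a third test is decided after baseline, during the treatment whose effect is being estimated. Fatigue and deconditioning are part of the phenomenon under study, and each test asks for cycling above lactate threshold. They are therefore plausible reasons for not coming back. If those who stop early tend to be those whose τ worsens most, the retained patients show less deterioration than the population the trial set out to describe. Recruiting replacements protects the count of 30 and the nominal power, but does not undo the selection.

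At stake is the main estimate, the change in τ and in the deltas per chemotherapy cycle. The rule governs the final analysis as a whole, so it also withholds early-cycle measurements from the comparisons between regimens.

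**Working it through.** **1. The plan's own figure.** The article states that a "sample size of at least n = 30 will be able to detect an effect of chemotherapy on τ with a power of 0.8". Its stated inputs are that "the random intercept will follow a gamma distribution with shape 1.57, a scale of 12.5, and a right shift of 13.25", and "a normal distribution of the error with standard deviation of 5.54". The mean slope, slope SD, number of cycles and alpha are not given, so n = 30 can be neither reproduced nor refuted. As a guide, take K equally spaced tests, two-sided alpha 0.05 (assumed) and a normal approximation:

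Var(slope per patient) = SD_slope² + 5.54²/Sxx

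detectable slope = (1.960 + 0.842) × √(Var/30)

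For K = 4, Sxx = 5. With SD_slope = 2, Var = 4 + 30.69/5 = 10.14, and the detectable slope is 2.802 × √(10.14/30) = 1.63 s per cycle. Over K = 3 to 7 and SD_slope 0 to 3, the detectable slope runs from 0.54 to 2.52 s per cycle. Many inputs fit n = 30.

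**2. How many patients could be left out.** Starters needed for 30 completers = 30/(1 − loss), rounded up. The loss rate is assumed.

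| Loss | Starters | Not completing |
|---|---|---|
| 10% | 34 | 4 |
| 20% | 38 | 8 |
| 30% | 43 | 13 |
| 40% | 50 | 20 |

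The article does not equate completing the study with three visits, so the last column only approximates the number the rule would exclude.

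**3. Effect on the slope.** The simulation uses the article's gamma intercept and error SD 5.54. The following are assumptions: true slope 2.0 s per cycle, linear in cycle; slope SD 1 or 2; 4 or 6 tests; 10 to 30% stopping after two tests; odds of stopping multiplied by 2 to 3 per SD of worsening.

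| Stopping depends on | Three-visit set | All data, random intercept and slope | All data, random intercept only |
|---|---|---|---|
| Nothing related to τ | 2.0 | 2.0 | 2.0 |
| Observed change in τ | 1.65–1.98 | 1.99–2.01 | 1.87–2.00 |
| Patient's underlying slope | 1.45–1.94 | 1.52–1.94 | 1.47–1.94 |

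In the second row, the three-visit set is low by 1 − 1.98/2.0 = 1% to 1 − 1.65/2.0 = 17.5%. All data came closer to the truth in every setting of that row.

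**4. Sensitivity to the assumed link.** Under another assumed form of the link to observed change (slope SD 2, 4 tests), the three-visit set gives 1.83, 1.68, 1.56 and 1.43 at 10, 20, 30 and 40% excluded. That is 8.5% to 28.5% too small, against 2.0 from all patients. The size is therefore set by assumption.

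**5. Set against sampling error.** SE of the mean slope with 30 patients = √(Var/30). For 6 tests and slope SD 1, Sxx = 17.5 and the SE is √((1 + 30.69/17.5)/30) = 0.30. For 4 tests and slope SD 2, it is √(10.14/30) = 0.58. The bias in the second row of step 3 is 2.0 − 1.98 = 0.02 to 2.0 − 1.65 = 0.35 s per cycle.

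**The case against.** The strongest reply is that nothing in the article shows that stopping is related to τ. It gives no dropout rate, no reasons for dropout and no slope. The rule counts visits, so a patient who deteriorates but attends three tests stays in, and so does one who asks to stop within a session. The rule also removes patients with short prescribed regimens or visits missed for unrelated reasons. Under the observed-change mechanism with the inputs of step 3, the bias is modest beside the standard error of a 30-patient pilot. If stopping follows the underlying slope, using all data recovers little. With the random-intercept model actually named, recovery is incomplete even under the milder mechanism.

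All of this stands, and it limits the point to a conditional one. It does not supply a reason for the rule, which discards measurements that the chosen model can use.

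Two stronger readings are tempting, but the article does not support them.

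- A reader might infer that tolerability in the analysed set is close to 100% by construction. Three visits are not the whole regimen: a patient who stops after the third test of a longer course is retained and counts as not tolerating it. Nothing says that feasibility will be computed in that set, and the data analysis section turns the first aim into change in mitochondrial capacity over cycles.
- A reader might infer that two sections disagree on what 30 counts, since trial status says "The study is planned to continue to enroll test subjects until n = 30". The sentence before it reports 26 participants who have completed, so 30 completers is the natural reading and agrees with the sample size section.

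**Conclusion.** The point holds in conditional form. The article fixes an inclusion rule that depends on attendance after baseline, gives no reason for it, and pairs it with a model that does not need it. If stopping after one or two tests is related to worsening τ, the estimated change per cycle is liable to be too small. Under the inputs of step 3, with stopping linked to the observed change, the three-visit set gives about 1.65 to 1.98 for a true 2.0 s per cycle. A stronger link or more exclusions give a larger shortfall. If stopping is unrelated to τ, there is no bias. Neither the size nor the presence of bias can be settled from the article, so it would be wrong to say that the result is biased.

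**What to change.** - Make all eligible participants with at least one on-off test the primary set for the mixed models. Fit the random intercept and slope already used in the power analysis, because an intercept-only model recovers less when stopping follows the observed change. Keep the three-visit set as a sensitivity analysis.
- State that this reduces the bias, but does not remove it if stopping depends on deterioration that was not observed.
- Report feasibility as retention and completion of scheduled tests, with reasons for stopping and exact 95% confidence intervals. The denominator should be eligible participants who started on-off testing. All consented participants would be the wrong denominator: consent comes before the visit 1 screening, and patients whose baseline cannot be done before treatment are waived, so both groups would count as failing to complete.

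The cost is a little more analysis work and some participants who contribute only one or two tests. No extra patients are needed. The trial is still collecting data, so the change can be made before the final analysis.
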